### Outcome model

Both the primary and secondary outcomes were compared using the IPW approach. The outcomes were compared using regression models with IPW and adjusted for unbalanced confounders after weighting. The analysis of PROs was conducted at 1-week, 3-weeks, 6-weeks, and 3-months after the index surgery adjusting for baseline scores.

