| Stone Clearance, %
(95% CI)                                                                                                                                                                                            | 72.4
(55.2-89.7)         | 72.1
(68.9-75.4) | 0.3
(-17.2-17.8)   |
| Stone size                                                                                                                                                                                                                 |                             |                     |                       |
| <7 mm                                                                                                                                                                                                                             | 53.2
(0.0-100.0)         | 78.6
(74.3- 83)  | -25.4
(-80.7-29.9) |
| 7-10 mm                                                                                                                                                                                                                           | 46.5
(0.0-100.0)         | 65
(58.5-71.6)   | -18.5
(-88-50.9)   |
| 10-15 mm                                                                                                                                                                                                                          | 75.5
(49.7- 100.0)       | 61
(50.4-71.6)   | 14.5
(-13.4-42.4)  |
| >15 mm                                                                                                                                                                                                                            | 92.5
(81.6-100.0)        | 57.1
(40.6-73.7) | 35.3
(15.5-55.1)   |
| Stone location                                                                                                                                                                                                             |                             |                     |                       |
| Lower pole kidney                                                                                                                                                                                                                 | 44.2
(3.3-85)            | 65.7
(57.8-73.6) | -21.5
(-63.1-20.1) |

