| Non-lower pole kidney                                                                                                                                                                                                             | 77.3
(54.9- 99.6)        | 57.8
(51.1-64.6) | 19.4
(-3.9-42.8)   |
| Ureter                                                                                                                                                                                                                            | 83.4
(54.1- 100.0)       | 81.1
(77-100.0)  | 2.2
(-27.3-31.8)   |

**eTable 12.** Stone Clearance for Percutaneous Nephrolithotomy (PCNL) and Ureteroscopy (URS) Considering Sensitivity and Specificity of Ultrasonographic Images on Centralized Imaging Review, Overall and by Stone Size and Stone Location

|                                        | Weighted PCNL vs URS |                     |                       |
|----------------------------------------|-----------------------------|---------------------|-----------------------|
|                                        | PCNL                 | URS          | PCNL-URS       |
| Stone Clearance, %
(95% CI) | 63.9
(41.8-86.1)         | 70.5
(66.2-74.7) | -6.5
(-29.1-16.1)  |
| Stone size                      |                             |                     |                       |
| <7 mm                                  | 48.9
(0.0-100.0)         | 78.1
(72.2-83.9) | -29.2
(-85.2-26.8) |
| 7-10 mm                                | 42.9
(0.0-100.0)         | 64.1
(55.7-72.5) | -21.2
(-89.9-47.5) |
| 10-15 mm                               | 65.5
(29.6-100.0)        | 59.3
(45.5-73.1) | 6.2
(-32.2-44.6)   |
| >15 mm                                 | 93.1
(81-100.0)          | 51.4
(29.1-73.7) | 41.7
(16.3-67.1)   |
| Stone location                  |                             |                     |                       |
| Lower pole kidney                      | 44
(0.7-87.3)            | 60.7
(50.5-70.9) | -16.7
(-61.2-27.8) |
| Non-lower pole kidney                  | 68.1
(38.4-97.9)         | 55
(45.9-64.2)   | 13.1
(-18-44.2)    |
| Ureter                                 | 72.5
(28-100.0)          | 81.2
(75.8-86.6) | -8.7
(-53.5-36.1)  |

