| eTable 13. Stone Clearance for Percutaneous Nephrolithotomy (PCNL) and Ureteroscopy (URS)
Based on Multiple Imputation for Missing Ultrasonographic Data at the 4- to 8-Week Interval,
Overall and by Stone Size and Stone Location |                             |                     |                       |
|--------------------------------------------------------------------------------------------------------------------------------------------------------------------------------------------------------------------------------------------------|-----------------------------|---------------------|-----------------------|
|                                                                                                                                                                                                                                                  | Weighted PCNL vs URS |                     |                       |
|                                                                                                                                                                                                                                                  | PCNL                 | URS          | PCNL-URS       |
| Stone Clearance, %
(95% CI)                                                                                                                                                                                                           | 66.7
(50.5-82.9)         | 73.1
(70.4-75.7) | -6.4
(-22.8-10)    |
| Stone size                                                                                                                                                                                                                                |                             |                     |                       |
| <7 mm                                                                                                                                                                                                                                            | 61.0
(16.4-100.0)        | 80.1
(75.1-85.1) | -19.1
(-63.6-25.4) |

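### In eTables 11-13 the overall PCNL clearance rates exceed what their own stone-size rows give under a balanced size mix, and the SAP adjusts for stone size only conditionally

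*Combined protocol and SAP*

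**What the plan says.** Protocol section 6.3 states that, given overlap, consistency and no unmeasured confounding, the weighted effects estimate population-average treatment effects. It says balance will be examined with the standardized difference in mean.

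The SAP (Propensity score model, eTable 1) puts stone size in the propensity model, but judges balance by a standardized difference in median. Only confounders above 0.25 after weighting go into the outcome model. Under Outcome model it says: "The outcomes were compared using regression models with IPW and adjusted for unbalanced confounders after weighting". Under the heterogeneity heading it says subgroup effects came from both stratified analyses and interaction models, without saying which fills the tables.

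eTables 11-13 are headed as weighted comparisons. The overall PCNL rows read "72.4 (55.2-89.7" (eTable 11), "63.9 (41.8-86.1" (eTable 12) and "66.7 (50.5-82.9" (eTable 13), each a rate with its 95% interval (closing bracket cut). In eTable 11 the overall URS row is "72.1 (68.9-75.4", and the first three PCNL size rows are "53.2 (0.0-100.0", "46.5 (0.0-100.0" and "75.5 (49.7- 100.0".

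**The concern.** If the overall row and the size rows use the same weights and no further adjustment, an arm's overall rate is the average of its size rows over that arm's weighted size mix. If weighting has balanced stone size to the population-average target, that mix is the pooled cohort's. The size rows and eTable 4 then predict the overall row, and for PCNL the prediction falls well short in all three tables.

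In eTable 4, 36 of 93 enrolled PCNL patients (38.7%) had a largest stone above 15 mm, against 43 of 946 URS patients (4.5%). The printed PCNL-URS difference also changes sign with size: in eTable 11 it runs from -25.4 points below 7 mm to +35.3 above 15 mm. An overall row with too much large-stone weight on the PCNL side would favour PCNL. It would also look more precise than the target allows, because the sparse small-stone PCNL patients would count for too little.

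**Working it through.** **Inputs.** eTable 4, largest stone size, enrolled patients, in the order <7, 7-10, 10-15, >15 mm:
- PCNL 15, 9, 20, 36, plus 13 with no stone or no size.
- URS 447, 246, 100, 43, plus 110 with no stone or no size.
- Pooled 462, 255, 120, 79 = 916 sized (50.4, 27.8, 13.1, 8.6%), plus 123 unlisted.

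The analytic cohort pools to 201, 137, 59, 34 of 431.

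PCNL size rows: eTable 11: 53.2, 46.5, 75.5, 92.5. eTable 12: 48.9, 42.9, 65.5, 93.1. eTable 13: 61.0, 41.9, 65.2, 81.1.

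**Step 1: the overall rate implied by the size rows.** Overall = sum of (share × row rate). For eTable 11: (462×53.2 + 255×46.5 + 120×75.5 + 79×92.5)/916 = 52,803.4/916 = 57.6%. The ceiling sets all 123 unlisted patients to cleared: (52,803.4 + 12,300)/1,039 = 62.7%.

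| | Printed PCNL | Enrolled mix | Analytic mix | Ceiling, enrolled | PCNL's own enrolled mix |
|---|---|---|---|---|---|
| eTable 11 | 72.4 | 57.6 | 57.2 | 62.7 | 75.7 |
| eTable 12 | 63.9 | 53.2 | 52.8 | 58.8 | 72.3 |
| eTable 13 | 66.7 | 58.0 | 57.1 | 62.9 | 68.9 |

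Every printed rate is above its ceiling and lies between the pooled-mix and own-mix values.

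**Step 2: the mix the printed rate needs.** Among the four sized bands, the smallest share above 10 mm that returns the printed rate puts all remaining weight in the <7 mm row and all large-stone weight in the >15 mm row:
- eTable 11: (72.4 - 53.2)/(92.5 - 53.2) = 49%
- eTable 12: (63.9 - 48.9)/(93.1 - 48.9) = 34%
- eTable 13: (66.7 - 61.0)/(81.1 - 61.0) = 28%

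The pooled share is (120 + 79)/916 = 22%.

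**Step 3: patients versus kidneys.** Clearance is analysed per kidney, while eTable 4 counts patients. eTable 6 sums to 98 PCNL units (58 + 33 + 7) and 1,070 URS units (485 + 479 + 98 + 8). Read as kidneys, that is 5 + 124 = 129 more than the 1,039 patients. If all 129 were above 10 mm, the pooled share would be (199 + 129)/(916 + 129) = 31%, short of eTables 11 and 12 but not of eTable 13. As a harsher test, let all 129 extra kidneys and all 123 unlisted patients clear. For eTable 11: (52,803.4 + 25,200)/1,168 = 66.8%. The same sum gives 63.3% for eTable 12 and 67.0% for eTable 13. eTable 11 remains 5.6 points short and eTable 12 only 0.6, while eTable 13 is no longer excluded.

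**Step 4: cross-checks.** The URS size rows on the pooled enrolled mix give 70.7, 69.4 and 71.8, against printed 72.1, 70.5 and 73.1. The PCNL location rows on the pooled enrolled location mix (189, 309, 470 of 968) give 73.8, 65.5 and 66.3, against 72.4, 63.9 and 66.7.

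**Step 5: the standardised difference.** PCNL minus URS on the pooled enrolled mix: 57.6 - 70.7 = -13.0 before rounding, 53.2 - 69.4 = -16.2, and 58.0 - 71.8 = -13.8. The half-width is the root sum of squares of (share × printed row half-width), treating strata as independent. For eTable 11 the terms are 27.9, 19.3, 3.7 and 1.7, giving 34.2. The others are 34.5 and 26.8. Printed half-widths are 17.5, 22.6 and 16.4. The rough intervals are -47 to 21, -51 to 18 and -41 to 13.

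**The case against.** The strongest reply is that the size rows need not average to the overall row. The SAP used stratified and interaction models for subgroups and allows extra covariates after weighting; rows from stratum-specific weights or separately adjusted models would break the identity without any imbalance. eFigure 4B shows balance by stone size but is not visible in this copy, and no document says whether size crossed the 0.25 threshold. This stands, and it rules out the tempting reading that the overall comparison is shown to be confounded by stone size.

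Three further points stand:
- The overall rates are not impossible given their rows. Each lies within its rows' range and is returned by a mix shifted toward large stones. The mismatch depends on taking the pooled cohort as target, which the protocol states for its three-arm model and the SAP does not restate for the two-arm tables.
- The cross-checks are modest support. URS is 946 of 1,039 patients, so its size rows would agree with almost no weighting. The eTable 12 location check does not discriminate: PCNL's own mix gives 62.1 and the pooled mix 65.5, either side of 63.9.
- The <7 and 7-10 mm PCNL rows rest on 15 and 9 enrolled patients (7 and 6 analytic), with intervals as wide as 0 to 100.

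The existing SAP rule is a weaker reply. Medians can agree while the upper tails differ, and the largest positive PCNL-URS differences are above 15 mm (35.3, 41.7 and 20.7 points). If separate models explain the gap, the tables set different estimands side by side without saying so.

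**Conclusion.** Under the pooled size mix that population-average weighting should produce, the printed PCNL overall rates exceed those implied by their size rows by about 15, 11 and 9 points, and exceed the most favourable patient-level treatment of unlisted patients by about 10, 5 and 4. The evidence is firmest for eTable 11 and weakest for eTable 13, where kidney-level counts could close the gap.

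The cause is open: excess large stones in the weighted PCNL arm, or different weights or models behind the rows. A reader might infer that PCNL truly clears fewer stones overall, or that the overall conclusion is overturned. The documents support neither, since the standardised intervals contain zero and the printed differences. What follows is narrower: the printed overall differences and their precision may not represent the stated target population.

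This rests on eTable 4 patient counts standing in for an unprinted kidney-level mix (enrolled and analytic versions agree within 1 point), on the 0-16 week sample having a similar mix, and on independent strata for the half-widths.

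**What to change.** In the SAP's Propensity score model and Outcome model sections, replace the conditional rule for stone size. Always include it in the weighted outcome model, as a spline or as the prespecified bands plus none and missing, and standardise to the cohort. Judge size balance by the standardized mean difference that the protocol specified and by the band shares.

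Report by arm the weighted size distribution (including no stone and missing) and the effective sample size. State which weights and model fill each row of eTables 11-13. Rerun the overall rows and print the size-standardised overall difference beside each. The overall row need not be forced to equal the average of its size rows, because separate subgroup models are legitimate when declared.

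The cost is SAP wording and a rerun on existing data. The downside is a wider overall interval, roughly 27 to 35 points either side on the approximation above.

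### eTables 11 and 12 print PCNL clearance limits that are too high for stones >15 mm, because the arm-level intervals behave as Wald intervals cut at 0% and 100%

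*Combined protocol and SAP*

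**What the plan says.** The SAP (Outcome model) compares outcomes by inverse-probability-weighted regression, with adjustment for covariates still unbalanced after weighting. Protocol section 6.3.2 plans weighted logistic regression and odds ratios with 95% intervals. Neither names a method for intervals on percentages or on differences in percentages, which is what eTables 11 to 13 report (row label "Stone Clearance, % (95% CI").

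Heterogeneity by stone size belongs to the primary objective (protocol 2.1) and to the SAP's heterogeneity section. Protocol 6.4 calls these analyses descriptive and not powered. eTable 11 (0–16 week window) and eTable 12 (misclassification correction) correspond to the SAP's sensitivity analyses. eTable 13 uses multiple imputation, which the SAP's Missing data section names for stone clearance.

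The relevant eTable 11 cells, quoted without their closing brackets, are:
- PCNL <7 mm: "53.2 (0.0-100.0"
- PCNL 7–10 mm: "46.5 (0.0-100.0"
- PCNL >15 mm: "92.5 (81.6-100.0"
- URS >15 mm: "57.1 (40.6-73.7"
- Difference >15 mm: "35.3 (15.5-55.1"

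In eTable 12 at >15 mm, PCNL is 93.1 (81 to 100.0), URS is 51.4 (29.1 to 73.7), and the difference is "41.7 (16.3-67.1".

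**The concern.** In eTables 11 and 12, 10 of the 14 PCNL stratum intervals end exactly at 0.0 or 100.0, and the difference intervals are symmetric about their estimates to rounding. That is the pattern of a Wald interval with impossible values cut away. Such an interval is unreliable when the proportion is near 100% and the sample is small, as with PCNL >15 mm. Cutting the upper end at 100 does not repair the lower end, which the symmetric construction places too close to the estimate. The >15 mm rows of eTables 11 and 12 hold the only stone-clearance differences in eTables 11 to 13 whose intervals exclude zero. A reader is therefore likely to use the PCNL lower limit there as a floor for what the procedure achieves.

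**Working it through.** **Inputs.** All figures are the printed estimates and limits in eTables 11 to 13, with z = 1.96. An arm SE is the half-width on a side not at a bound, divided by z.

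**1. Reproducing the >15 mm rows.**
- eTable 11: PCNL SE = (92.5 − 81.6)/1.96 = 5.56, so the uncut interval is 81.6 to 103.4 (printed 81.6 to 100.0). URS SE = (73.7 − 40.6)/(2 × 1.96) = 8.44. The difference half-width is 1.96 × √(5.56² + 8.44²) = 19.8, giving 35.3 ± 19.8 = 15.5 to 55.1, exactly as printed.
- eTable 12: PCNL SE = (93.1 − 81.0)/1.96 = 6.17, so the uncut interval is 81.0 to 105.2. URS SE = (73.7 − 29.1)/(2 × 1.96) = 11.38. The half-width is 25.4, giving 16.3 to 67.1, as printed.

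In these two tables the arm and difference SEs agree to rounding in every row, apart from one misprinted cell (step 6).

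**2. The 0.0–100.0 cells in eTable 11.** Both ends are at a bound, so SE_PCNL = √(SE_diff² − SE_URS²). Effective n = p(1 − p)/SE².
- <7 mm: √(28.21² − 2.22²) = 28.1, uncut −1.9 to 108.3, effective n = 3.1.
- 7–10 mm: √(35.43² − 3.34²) = 35.3, uncut −22.6 to 115.6, effective n = 2.0.

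With the same SEs, the logit scale gives 11.0–91.2 and 5.1–93.3, and Wilson gives 14.4–88.5 and 8.3–89.3. These stay within bounds but are still nearly uninformative.

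**3. Coverage of the PCNL >15 mm interval.** Effective n is 92.5 × 7.5/5.56² = 22.4 (eTable 11) and 93.1 × 6.9/6.17² = 16.9 (eTable 12). Treating these as binomial with n = 22 and n = 17, exact coverage of a nominal 95% Wald interval is about 82% and 70%; Wilson gives about 98% and 97%. Most of the shortfall comes from samples in which every kidney clears (0.925²² = 18%; 0.931¹⁷ = 30%), where the Wald interval collapses to a point at 100%. The observed strata are not in that state, so the shift in limits below is the more direct measure of the effect on the reader.

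**4. Replacement limits at >15 mm, same SEs.** On the logit scale, SE = SE_p/[p(1 − p)]. For eTable 11 this is 0.0556/0.0694 = 0.80, and 2.51 ± 1.57 transforms back to 71.9–98.3.

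| | Printed | Logit | Wilson |
|---|---|---|---|
| eTable 11, PCNL | 81.6–100.0 | 71.9–98.3 | 74.5–98.1 |
| eTable 12, PCNL | 81–100.0 | 67.2–98.9 | 71.6–98.6 |
| eTable 11, difference (MOVER) | 15.5–55.1 | 9.8–53.1 | 11.9–52.8 |
| eTable 12, difference (MOVER) | 16.3–67.1 | 8.6–63.7 | 12.2–63.0 |

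MOVER combines the arm limits. The lower limit is d − √[(p₁ − l₁)² + (u₂ − p₂)²]; with Wilson limits in eTable 11 this is 35.4 − √(18.0² + 15.0²) = 11.9, taking d as 92.5 − 57.1. Exact binomial coverage of the Wald difference is 93.4% (22 at 92.5% against 34 at 57.1%) and 94.0% (17 at 93.1% against 19 at 51.4%). Newcombe (MOVER with Wilson limits) gives 95.2% and 96.0%.

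**5. eTable 13.** At >15 mm the arm half-widths (36.9 and 14.85) combine to 39.8, but the printed difference half-width is 36.1. The relation in step 1 therefore does not hold there; separate pooling by Rubin's rules or t quantiles could explain it. The PCNL >15 mm interval is 44.2 to 118.0 uncut, so that limit is still cut at 100.

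**6. URS ureter, eTable 11.** The cell is 81.1 with limits 77 and 100.0. The lower half-width is 4.1, which implies an upper limit of 85.2. With the PCNL half-width of 29.3, √(29.3² + 4.1²) = 29.6, matching the printed difference half-width of (31.8 + 27.3)/2 = 29.55. A true 77–100 interval (half-width 11.5) would give 31.5.

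**The case against.** The strongest reply is that the treatment contrast is what matters, and it is barely touched. The difference is not near a bound and is not cut, its coverage is close to nominal, and zero stays excluded. That stands, so the point is confined to the arm columns.

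A reader might infer more, in four ways:
- **The >15 mm finding is an artefact of the interval method.** Not supported: in eTables 11 and 12 it survives both replacement methods.
- **The method is what makes the small strata uninformative.** Not supported: an effective n of 2–3 does that, and protocol 6.4 says these analyses are descriptive and need not be powered.
- **All three tables share the same construction.** Not supported: eTable 13 has no 0.0–100.0 cell, its SEs do not recombine, and its 10–15 mm upper limit is about 100.0 without any cutting.
- **The ureter cell is misapplied truncation.** Not supported: cutting at 100 cannot turn 85.2 into 100.0. eTables 12 and 13 print 86.6 and 87.9 for that cell, so it looks like an isolated printing error.

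It is also fair to say that the exact replacement limit depends on the method, and that Wilson with an effective n treats a weighted, adjusted estimate as a simple binomial. That is why ranges are given.

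**Conclusion.** The point holds for the arm-level intervals in eTables 11 and 12. For PCNL >15 mm the printed lower limits are too high by about 7–10 points (eTable 11) and 9–14 points (eTable 12). For the differences, the lower limits fall by about 4–8 points. No direction and no exclusion of zero changes. The multiple-imputation difference at >15 mm, 20.7 (−15.4 to 56.8), already covers zero as printed.

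The conclusion rests on these assumptions:
- The interval method is inferred from the figures, not stated.
- The replacements reuse the back-calculated SEs with a normal quantile, and inherit any error in those SEs.
- Coverage uses a simple binomial model at the effective n. Stratum denominators for the 0–16 week analysis are not given.

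The main-result table is not among the documents, so nothing follows about its intervals. The documents also do not single out the >15 mm result as their key finding.

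**What to change.** - State in the SAP that arm-level clearance percentages get intervals built on the logit scale from the weighted logistic model with robust SEs, or Wilson intervals with effective n. The logit option suits the logistic model already planned in protocol 6.3.2.
- Re-issue the arm columns of eTables 11 and 12. Optionally, report Newcombe/MOVER or bootstrap limits for the differences.
- For eTable 13, pool on the logit scale under Rubin's rules and transform back, so that limits stay within 0–100.
- Correct the eTable 11 URS ureter upper limit to its computed value (about 85).

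The cost is a sentence or two in the SAP, a re-run of existing models for the arm columns, and one corrected cell. No new data are needed.

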### Missing data

We used multiple imputation (MI) to handle missing data. Variables used to impute missing data included all baseline covariates, treatment variable, and observed outcomes that were used in the analysis. Twenty imputed datasets were created and analyzed separately, and the results were combined using Rubin's rules to produce valid statistical inferences. MI was used for the analyses of stone clearance, PROs at week 1, and HTE of both primary and secondary analyses.

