|                                                                                                                                                                  | My hospital rents a shockwave lithotripter (e.g. mobile unit). | 28
(90.3)                  | 984
(94.7)                                                                   |
| Provides off-hours access (after 5:00pm on weekday and weekend) to a shockwave lithotripter, No. (%)                                                             |                                                                | 3
(9.7)                    | 82
(7.9)                                                                     |
| Interventional Radiology available 24 hours a day, 7-days a week at hospital, No. (%)                                                                            |                                                                | 31
(100)                   | 1039
(100)                                                                   |
| Have a multi-disciplinary kidney stone clinic, No. (%)                                                                                                           |                                                                | 19
(61.3)                  | 720
(69.3)                                                                   |
| IQR: interquartile range; ICD: international classification of disease; ED: emergency department; PCNL: percutaneous nephrolithotomy; SWL: shockwave lithotripsy |                                                                |                               |                                                                                 |

**eTable 4.** Characteristics of the Enrolled and Primary Analytic Cohorts of Patients Who Underwent Percutaneous Nephrolithotomy (PCNL) and Ureteroscopy (URS)

|                                                  |                               | PCNL                    |                              | URS                     |                               |
|--------------------------------------------------|-------------------------------|-------------------------|------------------------------|-------------------------|-------------------------------|
| Characteristics                                  |                               | Enrolled Cohort (93)    | Primary Analytic Cohort (46) | Enrolled Cohort (946)   | Primary Analytic Cohort (436) |

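### The overall URS interval in eTable 13 is as narrow as if every treated kidney had been scanned, which does not fit the Rubin's-rules pooling that the SAP states

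*Combined protocol and SAP*

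**What the plan says.** The Missing data section of the SAP (eAppendix 1) describes 20 imputed datasets analysed separately, after which "the results were combined using Rubin's rules to produce valid statistical inferences". It applies multiple imputation to stone clearance, to week-1 PROs and to the heterogeneity analyses. The imputation model uses baseline covariates, treatment and the observed outcomes in the analysis. The SAP section on the study unit makes the kidney the unit for stone clearance.

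eTable 13 reports stone clearance after imputation of missing 4- to 8-week ultrasounds. The overall row gives URS "73.1 (70.4-75.7"), PCNL "66.7 (50.5-82.9") and a PCNL minus URS difference of -6.4 (-22.8 to 10).

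Three other tables allow a check.

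- eTable 4 gives the cohort sizes: URS "Enrolled Cohort (946") and "Primary Analytic Cohort (436"); PCNL "Enrolled Cohort (93") and 46 in the primary analytic cohort.
- eTable 11, with images from 0 to 16 weeks, gives URS "72.1 (68.9-75.4").
- eTable 12, corrected for misclassification, gives URS "70.5 (66.2-74.7").

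No table reports a within- or between-imputation variance or a fraction of missing information.

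**The concern.** Rubin's total variance adds a between-imputation term to the average within-imputation variance. With roughly half the outcomes imputed and predictors of ordinary strength, that term brings the SE back close to the complete-case value. The overall URS interval shows no sign of it.

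eTable 13 is where a reader learns how far the stone-clearance result depends on missing ultrasounds. If its overall row leaves out the uncertainty from imputation, it overstates precision. If the PCNL cell has the same fault, it also understates how large a PCNL-URS difference remains compatible with the data.

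**Working it through.** **Inputs.** Printed intervals come from eTables 11, 12 and 13, and enrolled and analytic counts from eTable 4. eTable 6 gives the URS kidneys: 485 + 479 + 98 + 8 = 1,070. The number of imputations, 20, is from the SAP.

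**1. Precision of the printed URS interval.** SE = (upper - lower)/3.92 = (75.7 - 70.4)/3.92 = 1.35 points. Effective n = p(1-p)/SE² = 0.731 × 0.269/0.01352² = 1,076. Rounding of the limits allows 1,036 to 1,117.

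**2. Reproducing it as fully observed data.** With n = 1,070, SE = √(0.731 × 0.269/1,070) = 1.356 points, giving 70.4 to 75.8. This matches the printed interval to 0.1 point. With 946 patients as the unit, full observation gives 70.3 to 75.9, already slightly wider than printed. The implied fraction of missing information is zero, or at most about 3% after rounding.

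**3. Share observed.** 436/946 = 46.1%, so 53.9% of URS patients are outside the primary analytic cohort. Treating the cohort as those with a 4- to 8-week outcome is an inference. It is supported by eTable 12, where the URS SE is (74.7 - 66.2)/3.92 = 2.17 and the effective n is 442.

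**4. Comparison with real scans.** In eTable 11 the URS SE is (75.4 - 68.9)/3.92 = 1.66, with an effective n of 732. The imputed analysis therefore claims more precision than the analysis that widens the window to use more actual images.

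**5. Strata against the overall row.** The recombined SE is √Σ(nᵢ·SEᵢ)²/Σnᵢ. The weights are the enrolled URS counts in eTable 4 (size 447/246/100/43, sum 836; location 164/256/457, sum 877), and strata are treated as independent. The eTable 11 ureter upper limit, printed as 100.0, is taken as 85.2 by symmetry.

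| Table | By size | By location | Overall row |
|---|---|---|---|
| eTable 11 | 1.73 | 1.66 | 1.66 |
| eTable 12 | 2.28 | 2.21 | 2.17 |
| eTable 13 | 1.86 | 1.65 | 1.35 |

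For eTable 13 the stratum SEs are 2.55, 2.93, 6.91 and 7.58 by size, and 4.87, 3.32 and 1.86 by location. Giving every unclassified patient zero variance (dividing by 946 instead) still leaves 1.64 and 1.53.

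**6. What Rubin's rules should give.** T = W + (1 + 1/M)B, with W = 0.731 × 0.269/1,070 = 1.838 × 10⁻⁴, M = 20 and B = W·g/(1-g), where g is the fraction of missing information.

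- Weak predictors, g = 0.539: B = 2.150 × 10⁻⁴ and √T = 2.02 points. The interval is about 69.1 to 77.1, half-width about 4.0.
- 0- to 16-week scans as perfect surrogates, g = 1 - 732/1,070 = 0.316: √T = 1.65 points. The interval is about 69.8 to 76.4, half-width about 3.2 to 3.3.

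The printed half-width is 2.65.

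**7. Could good predictors explain it?** Applying 46.1% to 1,070 kidneys gives about 493 observed. The variance is then about p(1-p)[R²/1,070 + (1-R²)/493]. The SE is 1.83 at R² = 0.3, 1.71 at 0.5 and 1.38 at 0.97. Reaching the printed width needs R² of about 0.97 or more. The URS rates in eTable 13 by location explain about 7% of outcome variance, and by size about 4%. In 400 simulated Rubin analyses using location, the half-width averaged 3.9 and was never below 3.0.

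**8. PCNL and the difference (indicative only).** The printed SEs are 8.27 and 8.37. eTable 12 gives a PCNL SE of 11.30, a design effect of 0.1130²/(0.639 × 0.361/46) = 2.55. Carried to 93 patients, this gives an SE of 7.8 if all were observed and about 11.2 under Rubin's rules. The difference would then have SE √(11.23² + 2.02²) = 11.4 and a half-width of 22 to 23, against 16.4 printed.

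**The case against.** A reader might infer that the between-imputation variance was simply dropped. The documents do not establish this. Dropped variance, stacked datasets, single imputation and a transcription error would look alike in print. The match to 1,070 kidneys is also not proof of mechanism, because it sets an unweighted binomial SE against a weighted estimate. Scaling by eTable 12's ratio of effective to observed kidneys (442/493, itself an assumption) gives a within-only SE of about 1.43. The printed 1.35 is below even that, so this weakens the diagnosis but not the inconsistency.

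A reader might also infer that all of eTable 13 is faulty. The subgroup rows do not support that. Effective n against enrolled URS patients is 245 of 447 (<7 mm), 51 of 100 (10-15 mm) and 97 of 164 (lower pole), all wide enough to include imputation uncertainty. Two PCNL rows (>15 mm and non-lower pole) are wider than in eTable 12. On the other hand, URS 7-10 mm (257 of 246) and >15 mm (42 of 43) look fully observed. The pattern is mixed.

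It is tempting, too, to say that the PCNL and difference intervals under-cover. That is not shown. The benchmark in eTable 12 also contains the misclassification correction, and the printed PCNL SE of 8.27 lies above the full-data figure of 7.8.

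The observed number of kidneys is not stated, and scans outside the window could have informed the imputation; the range in step 6 allows for the latter. Finally, the SAP's pooling rule is itself correct, and the difference interval already includes zero. All of this stands. None of it explains an overall URS interval narrower than that of eTable 11 and of its own strata.

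**Conclusion.** The printed overall URS interval is incompatible with the pooling that the SAP describes. Its half-width of 2.65 points should be about 3.2 to 4.0. The between-imputation variance appears to be missing from that row, but the cause is unknown.

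The URS result rests on the printed limits, the eTable 6 kidney count and the inference that about 46% of URS outcomes were observed. The strata comparison does not need that inference, though it uses enrolled patient counts as weights and treats strata as independent.

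For PCNL and the difference, the intervals may be too narrow. The 22 to 23 point half-width for the difference is only a guide, because it assumes that eTable 12's design effect carries over. The overall conclusion of no demonstrated difference does not change; the stated precision does.

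**What to change.** Recompute the overall row of eTable 13 for URS, PCNL and the difference with T = W + (1 + 1/M)B. Here W is the mean robust variance of the weighted estimate across imputed datasets, and B is the variance of the 20 estimates. Report W, B and the fraction of missing information, and replace the printed intervals. State how many kidneys in each arm had an observed 4- to 8-week outcome.

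Check the subgroup rows of eTable 13 and the other analyses that the SAP assigns to multiple imputation (week-1 PROs and heterogeneity) for the same fault.

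The cost is a re-run on existing data and wider intervals. No new data are needed.
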